## Abstract

**Background:**

One third of women experience intimate partner violence (IPV) in their lifetime. Orthopaedic health care professionals are in a good position to identify women experiencing escalating physical violence and act to promote their immediate safety, connect them to IPV resources, and reduce the risk of further harm. However, there have been no studies that explore whether experiencing a musculoskeletal injury can trigger or worsen IPV, and there have been no studies on how experiences of IPV affect orthopaedic outcomes. The primary objective of the PRAISE-2 pilot study is to assess the feasibility of conducting a large cohort study to determine the association between IPV and injury-related complications. The secondary clinical objectives are to preliminarily explore how a history of IPV affects orthopaedic outcomes and how patterns of IPV change over time following an orthopaedic injury.

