#### Clinical objectives

Clinical objectives in this pilot study are exploratory. The clinical objectives of the PRAISE-2 study include determining (1) how a history of IPV affects injury-related complications; (2) how a history of IPV affects return to pre-injury function; (3) incident cases of IPV after a musculoskeletal injury if the injury was not the result of IPV; (4) how a history of IPV affects health care and support service use after a musculoskeletal injury; (5) how a history of IPV affects health-related quality of life after a musculoskeletal injury; (6) how patterns of IPV change over time after a musculoskeletal injury; and (7) how abused women’s stage of change (i.e. readiness to make changes to move toward a life free from violence) changes over time after a musculoskeletal injury.

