#### Patient screening and enrolment

All new female patients (within 6 weeks of injury) presenting to the fracture clinics of participating surgeons will be screened for participation in this study. A female research coordinator will approach each potentially eligible female patient and screen each patient for eligibility. The female research coordinator will obtain informed consent from each eligible patient who wishes to participate. Since this study will record change in IPV status over time, and we plan to make comparisons to a non-abused control group, we will follow all eligible and consenting patients regardless of whether they report experiencing IPV at baseline. We will record numbers of excluded and missed patients, and reasons for exclusion.

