#### Secondary (clinical) outcomes

Since this is a pilot study, clinical outcomes will be exploratory. Clinical outcomes are (1) injury-related complications; (2) return to pre-injury function; (3) new IPV disclosures; (4) utilization and associated costs of health, legal, and social support services; and (5) changes in abuse severity/frequency and type of abuse (physical, emotional, and/or sexual IPV); (6) health-related quality of life; and (7) stage of change.Injury-related complications—Injury-related complications are adverse effects that are related to sustaining the injury or the treatment for the injury. These include bone healing problems, infection, unplanned additional surgical procedures or hospitalizations, mortality, and problems with the surgical implants requiring medical intervention. An orthopaedic surgeon who is blinded to identifying details and IPV status will adjudicate whether the event is injury-related.Return to pre-injury function—We will use the Return to Function Questionnaire (RTF) which is a four-question tool that was used in a recently completed large FDA-regulated fracture trial [28].New IPV disclosures—Women’s self-reported experience of IPV will be measured using a direct method of screening used by the PRAISE Investigators [14, 15] in two previous studies conducted in trauma populations. The tool comprises three questions with three response options (Table 2). This tool has proven feasible to administer in a trauma population and has been shown to have greater sensitivity to identify IPV compared to the partner violence screen (PVS) [29]. It is important to maximize sensitivity when screening IPV victims because not identifying victims can have many negative health and social consequences [30]. The direct method of screening can also distinguish between types of IPV (i.e. physical, sexual, and emotional abuse). A participant will be considered to have disclosed IPV if she answers positively to at least one of the three direct screening questions.Use and associated costs of health, legal, and social support services—Women’s access to and use of health and support services will be measured by directly asking participants to self-report if they have accessed health care services, a social worker, mental health professional, women’s shelter, helpline, violence against women website, or legal assistance. We will further ask participants whether they have referred a friend or family member to any of the IPV services. We will conduct a cost analysis from a societal perspective using a 1-year time horizon. Total and incremental costs will be reported as 2018 Canadian dollars for women with and without a history of IPV. Direct costs will be estimated from costs associated with injury-related complications and additionally derived from utilization of health care, social work, and mental health services. Indirect costs will be estimated from loss of productivity and time to return to function.Changes in abuse type and severity/frequency—Using the direct method of screening (Table 2), which categorizes types of violence as physical, emotional, and/or sexual abuse, we will record and analyze changes in type and severity/frequency of IPV experienced over time. Participants will be classified as experiencing no abuse, stable level of abuse, escalating abuse, and de-escalating abuse.Health-related quality of life—Participants’ quality of life will be measured using the EuroQol-5 Dimensions (EQ-5D), a widely used and well-validated quality of life tool [31]. The EQ-5D is a comprehensive, five-item compact health status classification and health state preference questionnaire.Stage of change—Participants will complete the Domestic Violence Survivor Assessment (DVSA) Short Form questionnaire to determine her stage of change. The stages of change are based on the transtheoretical model of health behaviour change applied specifically to survivors of abuse [32]. The stages of change are (1) Pre-contemplation: committed to continuing the relationship, change is not contemplated; (2) Contemplation: committed but questioning/contemplating change; (3) Preparation: considering change/exploring options to end abuse; (4) Action: victim breaks away from abusive relationship or partner stops being abusive, and (5) Maintenance: establishment of a new life apart or together. The original DVSA is well-used in IPV research and counselling and has been determined to be feasible to administer, reliable, and sensitive to change [33]. We developed the DVSA Short Form for the purpose of this study, with the aim of making the self-administered form more accessible and less time-consuming to administer in a research setting (e.g. removed gendered pronouns, removed references to having children, simplified language, removed two redundant/obsolete questions). Depending on the findings regarding feasibility of administration, we may conduct validation studies in the future.

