#### Secondary analyses

The analyses of clinical outcomes will be exploratory in nature since the primary focus is on assessing feasibility. We will therefore not present *p* values for comparative analyses. We will not carry out any imputation for missing data in this pilot study.Injury-related complications—We will present proportions of patients experiencing injury-related complications in each group (i.e. women with and without a history of IPV) over 12 months with 95% CI. We will also perform an exploratory logistic regression analysis.Return to pre-injury function—We will report the proportion of patients achieving return to pre-injury level of function in each group at baseline, 3 , 6 , and 12 months with 95% CI. We will also perform an exploratory logistic regression analysis.New IPV disclosure*—*New IPV disclosures will be reported as an incidence statistic with 95% CI.Utilization and costs of health, legal, and social support services—Will be reported descriptively as proportions of women using each service per group over 12 months as well as the median number of times that participants used each service with interquartile range (IQR). Direct costs will be derived by assigning costs to adjudicated injury-related complications and self-reported utilization of health care services based on provincial case costing registries and health care provider schedule of benefits. All remaining direct costs will be estimated by multiplying self-reported units of utilizations (e.g. visits to social worker, use of mental health services) by an estimate of the cost per unit of service based on provincial or national average charges. Indirect costs will be calculated using self-reported annual income and return to function. Costs will be presented as means with 95% CIs, and histograms. Due to the non-normality of cost data, non-parametric bootstrap estimates will be used to present the difference in mean costs between those with and without a history of IPV. Multivariable sensitivity analysis will be conducted by using 95% CI and reported cost ranges for input parameters. All costs will be inflated to 2018 Canadian dollars using the appropriate price indices.Changes in IPV type and severity—We will report the proportion of patients who experienced no abuse over 12 months, a stable level of abuse over 12 months, escalating abuse, and de-escalating abuse over 12 months with 95% CI. We will present this graphically.Health-related quality of life—We will report the mean change in HRQL from baseline to the 3-, 6-, and 12-month visits by group with 95% CI. We will also estimate utility, which will be modelled over the course of 1-year follow-up, using 3-, 6-, and 12-month EQ-5D scores and standard trapezoidal rules. Utility will be presented as quality adjusted life years (QALYs) for each group, with 95% CI, where 1 represents full health and 0 represents death. The difference between each group will be presented as QALYs lost.Stages of change—We will report the change in stage of change from baseline at 3, 6, 9, and 12 months for patients who report that their current relationship is or was abusive.

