## Discussion

Previous studies have assessed physical health outcomes of IPV victims, but they are limited by their cross-sectional design and by only assessing general physical health outcomes. Based on the international attention earned by the original PRAISE study [14], we believe that orthopaedic surgeons and others who treat injured women are interested in gaining insight into how IPV affects their patients’ injury-related outcomes. This pilot study will begin to fill some of the gaps in the literature faced by health care professionals who treat injured women who have experienced IPV. It will also provide much-needed feasibility data for recruiting, following, and measuring outcomes in a longitudinal IPV study of injured women in a fracture clinic setting.

We believe a pilot study is a critical step to ensure feasibility of future longitudinal IPV research among injured women. In previous studies of IPV victims, patient follow-up has typically been difficult, with one large otherwise high-quality trial losing almost 40% of their study sample over 18 months. We propose a plan to minimize loss to follow-up (Fig. 2) based on the strategies developed by Logan et al. [36] and adapted by Madden et al. [37], and we will take this opportunity to test and refine this strategy. We will use the information gained in the pilot study to determine the feasibility of a larger definitive study and to refine recruitment, follow-up, measurement, and data collection strategies that will be useful in not only prospective cohort studies in this population, but also future planned interventional research in our IPV research program. The ultimate goal of our research program in IPV is to reduce further violence and injuries. We aim to accomplish this by evaluating an identification and support program for victims of IPV in fracture clinics. Health care professionals, researchers, and health policy makers require high-quality, evidence-based information to guide their decisions. The current pilot prospective cohort will begin to fill some of these gaps in knowledge. In order for a screening and support program to be successful, health care professionals need to understand whether having a musculoskeletal injury can lead to new or worsening IPV, how patterns and types of IPV can change over time, and the types of services victims utilize, have access to, and need.

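### The IPV-change outcome is reported over all patients without a split by baseline IPV status, so, if change is judged against baseline, its 'escalating' proportion mixes first onset with worsening and does not show what happens to women already abused

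*Protocol article*

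**What the plan says.** Under Secondary (clinical) outcomes, the item on changes in abuse type and severity/frequency states: "Participants will be classified as experiencing no abuse, stable level of abuse, escalating abuse, and de-escalating abuse". Under Secondary analyses the report is fixed as "the proportion of patients who experienced no abuse over 12 months, a stable level of abuse over 12 months, escalating abuse", and then de-escalating abuse, with 95% CIs and a graph. Table 3 repeats this. None of the three places splits or restricts the outcome by baseline IPV status.

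The cohort is mixed by design. Patient screening and enrolment says "we will follow all eligible and consenting patients regardless of whether they report experiencing IPV at baseline".

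The outcome serves clinical objective 6, "how patterns of IPV change over time after a musculoskeletal injury". Onset is a separate objective (number 3), "incident cases of IPV after a musculoskeletal injury if the injury was not the result of IPV", reported as an incidence with 95% CI under new IPV disclosures.

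The last item of Secondary analyses, stages of change, is limited to patients who report that their relationship is or was abusive. The IPV-change item carries no such limit.

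**The concern.** Onset and worsening have different risk sets. Only a woman free of IPV at baseline can have a first onset; only a woman with IPV at baseline can have it worsen or ease. The article treats both as worth knowing. The abstract names as a gap "whether experiencing a musculoskeletal injury can trigger or worsen IPV", and the Discussion says professionals need to understand "whether having a musculoskeletal injury can lead to new or worsening IPV".

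With one all-patient denominator, the *escalating* proportion draws on both risk sets while *de-escalating* draws mainly or wholly on one. The two figures will stand side by side in a table and a graph, and a reader will compare them. At stake is the interpretation of the result, and its value for planning the larger study that this pilot is meant to inform.

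**Working it through.** **Inputs from the article (Sample size determination).** N = 250; past-year IPV 1 in 6; lifetime IPV 1 in 3. There is no stated figure for this outcome to reproduce.

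**Inputs assumed.** The documents give no rates of onset, worsening or improvement. Those below are illustrations.

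**Step 1: where onset falls.** Take a woman who answers 'Never' at baseline and 'Sometimes' or 'Often' later (Table 2 response options), with change judged against baseline. She did not have 12 months without abuse, she is not stable, and she is not de-escalating. *Escalating* is the only label left. This is by elimination; the article does not say it.

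**Step 2: size of the risk sets.** 250/6 ≈ 42 women with past-year IPV at baseline; 250 − 42 = 208 without. On this reading the 208 can only remain at no abuse or become *escalating*, and only the 42 can be *stable* or *de-escalating*.

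**Step 3: one worked case.** Assume 8 of the 42 worsen, 13 improve, 21 are unchanged, and 10 of the 208 report new abuse. Intervals are Clopper-Pearson 95%.

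| | Escalating / worse | De-escalating / better | Onset |
|---|---|---|---|
| All patients, as planned | (8 + 10)/250 = 7.2% (4.3–11.1) | 13/250 = 5.2% (2.8–8.7) | inside *escalating* |
| IPV at baseline | 8/42 = 19.0% (8.6–34.1) | 13/42 = 31.0% (17.6–47.1) | – |
| No IPV at baseline | – | – | 10/208 = 4.8% (2.3–8.7) |

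The pooled point estimates suggest more worsening than easing; among abused women the order is the other way round. Onset supplies 10 of the 18 *escalating* women (56%). The intervals overlap in both presentations.

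**Step 4: when the order reverses.** Pooled *escalating* exceeds pooled *de-escalating* once onset among unabused women passes (number improving − number worsening) / (number unabused).

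| Worsening / improving (assumed) | Past-year: 42 and 208 | Lifetime: 83 and 167 |
|---|---|---|
| 30% / 35% | (15 − 13)/208 = 1.0% | (29 − 25)/167 = 2.4% |
| 20% / 30% | (13 − 8)/208 = 2.4% | not computed |
| 20% / 40% | (17 − 8)/208 = 4.3% | (33 − 17)/167 = 9.6% |
| 10% / 50% | (21 − 4)/208 = 8.2% | (42 − 8)/167 = 20.4% |

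Reversal is not automatic. In the 20%/40% past-year case, onset of 2% (4 women) gives *escalating* (8 + 4)/250 = 4.8% against *de-escalating* 17/250 = 6.8%: no reversal.

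**Step 5: dependence on prevalence.** This needs no onset rate. A constant 20% worsening risk among abused women contributes 0.20 × 1/6 = 3.3% of the cohort at a prevalence of 1 in 6, and 0.20 × 1/3 = 6.7% at 1 in 3.

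**The case against.** The strongest reply has four parts.

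*Onset is covered elsewhere.* This stands. New IPV disclosures have their own objective, outcome and analysis. A reader might infer from the pooling that the plan answers neither the onset question nor the worsening question; the documents do not support that for onset. What no other listed outcome gives is worsening or easing among women already abused.

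*The article never defines escalating.* This stands in part. Category rules may be left to a fuller document. Step 1 assumes comparison with baseline. IPV is assessed at five visits, and a rule based on the trajectory could call a woman with 'Never', then 'Often', then 'Sometimes' de-escalating, or one with 'Sometimes' at every visit after baseline stable. So it cannot be said that the pooling into *escalating* holds under any scoring. A trajectory rule would not remove the mixing, though: it would move some onset cases into the other labels, still over all patients. And the finding is not the missing rule; it is the denominator that the article does state.

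*Little is lost, because the split can be recovered.* With a baseline count and no attrition, worsening in Step 3 is 42 − 21 − 13 = 8. The individual data also remain and can be tabulated either way, so a reader who concluded that the result is unusable for the definitive study would go too far. But the recovery needs the baseline count for the women actually classified and a strict baseline rule, neither of which is part of the stated report. Nor is subtracting new disclosures from *escalating* clean: objective 3 conditions on the injury not being due to IPV rather than on absence of IPV at baseline, and any positive answer counts as a disclosure.

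*The outcome is exploratory.* This stands. There are no p values, no feasibility criterion depends on it, by-site reporting is specified only for the feasibility outcomes, and no formal contrast of escalating with de-escalating is planned. The effect is on interpretation.

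**Conclusion.** The concern holds in a limited form. The article reports four proportions of all patients, in a cohort mixed at baseline. If change is judged against baseline, *escalating* pools onset among about 208 women with worsening among about 42. That proportion moves with IPV prevalence and cannot be read as worsening among abused women, and no other listed outcome fills that gap.

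A reader might infer that the planned report will show the reverse of what abused women experience. The documents do not support that as a prediction. It needs onset above a threshold of roughly 1–4% for 20–30% worsening and 30–40% improving under the past-year definition, and higher in other cases (8.2% for 10%/50%; up to 20.4% under the lifetime definition). All these rates are assumptions. Dependence on prevalence does not need them.

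This should be changed, because it alters the reported figures and their intervals at almost no cost. It does not threaten the pilot's primary feasibility outcomes.

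**What to change.** In Secondary (clinical) outcomes, Secondary analyses and Table 3, report the IPV-change outcome by baseline IPV status, each group with its own denominator and 95% CI:

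- women without IPV at baseline: no abuse / new onset;
- women with IPV at baseline: stopped or decreased / stable / increased.

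State whether baseline status means past-year or lifetime IPV. Reserve the terms escalating and de-escalating for the second group, and draw the planned graph separately for the two groups. The all-patient distribution may be kept alongside as a description of the cohort.

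The cost is wording only. IPV status is already collected at every visit (Table 1), so there is no added burden on participants. The intervals for women with IPV at baseline will be wider, since they rest on about 42 women (for example 8.6–34.1% around 8/42), which is the precision that the study actually has for that question.

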### Study follow-up

Participants will complete the questionnaires in the surgical clinic (baseline), and at 1, 3, 6, and 12 months after the baseline assessment. Participants will be provided with the option of completing the study questionnaire in the clinic or over the telephone (Fig. 1). Table 1 lists the assessments at each study time point. We chose a 12-month follow-up period because this is the most common follow-up length in other IPV studies [34].

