### Patient selection

#### Eligibility criteria

We will use broad eligibility criteria to increase the generalizability of the study. The inclusion criteria are (1) adult females (at least 16 or 18 years of age depending on local ethics requirements); (2) patients presenting to participating fracture clinics within 6 weeks of their injury; and (3) patients presenting with a fracture or dislocation which is being managed with either surgical or non-surgical treatment.

The exclusion criteria are (1) unwilling to or unable to provide consent; (2) unable to complete the study questionnaires in a private location, due to safety and confidentiality; (3) unwilling or unable to follow the study protocol or their attending surgeon has concerns about their ability or willingness to follow study protocols; and (4) does not speak and write in English or the dominant language of the local clinic. Due to the sensitive nature of the topic, only patients who can consent for themselves will be considered for participation.

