### Study outcomes

#### Primary (feasibility) outcomes

The primary outcome of the pilot study is feasibility including recruitment, adherence to visit windows, participant retention, and data completeness. The criteria for success of feasibility are as follows:Recruitment—Our recruitment strategy will be considered feasible if each site is able to recruit 50 participants in 12 months or less after their training call/visit.Adherence to visit windows—We have attempted to align study visit windows with clinical standard of care visits; however, standard of care visits can vary by region and/or type of injury. We expect that at least 75% of study visits should be within the defined windows in Table 1.Participant retention—While 20% loss to follow-up has traditionally been considered the industry standard [26], there is evidence from orthopaedic studies that bias begins to affect study results at even lower rates of loss to follow-up [27]. Therefore, our loss to follow-up minimization strategy will be considered feasible if loss to follow-up remains under 15%.Data completeness—Based on our experience in previous multicentre orthopaedic trauma studies, we are typically able to obtain questionnaire completeness rates of 75–85% at 12 months. Therefore, we will consider our data collection strategies to be feasible if questionnaire completion remains over 80%.

**Table 1 Tab1:** PRAISE-2 schedule of events

Assessment	Baseline (0–6 weeks from injury)	1 month (2–6 weeks from injury)	3 months (11–15 weeks from injury)	6 months (24–28 weeks from injury)	12 months (48–56 weeks from injury)
Target visit window					
Screening form	X				
Informed consent	X				
Demographic characteristics form	X				
Injury characteristics form	X				
IPV status (type, frequency, severity)	X	X	X	X	X
Assessment for complications	X	X	X	X	X
Support service utilization	X	X	X	X	X
Return to function	X	X	X	X	X
EQ-5D	X	X	X	X	X
Stages of change	X	X	X	X	X
Radiograph	(X)	(X)	(X)	(X)	(X)
Clinic notes	(X)	(X)	(X)	(X)	(X)

(X) = Only if required to adjudicate an adverse event

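### Follow-up is scheduled from baseline, but the windows that score adherence run from injury; the two clocks can differ by up to 6 weeks and must be reconciled

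*Protocol article*

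**What the plan says.** Two sections of the protocol article give the follow-up visits different starting points.

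- **Study follow-up** has questionnaires completed at baseline and then "at 1, 3, 6, and 12 months after the baseline assessment". It cites Table 1 only for the list of assessments at each time point.
- **Table 1**, under Primary (feasibility) outcomes, sets every target window from injury. The enrolment column reads "Baseline (0–6 weeks from injury", and the first follow-up column is headed "1 month (2–6 weeks from injury". The three later columns use the same origin, with limits of 11–15, 24–28 and 48–56 weeks for the 3-, 6- and 12-month visits.
- **Eligibility criteria** admit "patients presenting to participating fracture clinics within 6 weeks of their injury", so baseline may legitimately fall anywhere in those 6 weeks.
- **The adherence criterion**, one of four primary feasibility outcomes, is that "at least 75% of study visits should be within the defined windows in Table 1". Sample size determination expects a figure above 80%.

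Two further statements bear on the choice of origin. The adherence paragraph says the windows were set with standard-of-care visits in mind. Maximizing patient follow-up says study visits will coincide with routine fracture clinic visits.

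**The concern.** The baseline clock and the injury clock differ for each woman by her time from injury to enrolment, which may be as long as 6 weeks. The 1-, 3- and 6-month windows are only 4 weeks wide and the 12-month window 8 weeks wide. A site that follows the Study follow-up text exactly can therefore produce visits that Table 1 scores as out of window.

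At stake is the meaning of a primary pass/fail result. To the extent that sites schedule from baseline, the adherence percentage mixes two things: whether women attend when due, and how soon after injury they were enrolled. A figure below 75% could not then be read as poor attendance, and the pilot exists to tell a larger study whether its visit schedule is workable.

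The second difficulty does not depend on which clock sites use. The 1-month window (2–6 weeks) sits entirely within the baseline window (0–6 weeks), so the two visits can coincide, and the 1-month window can open, or close, before a late enrollee has had her baseline visit.

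**Working it through.** The plan gives no calculation of expected adherence from its own schedule. It states only the belief that adherence will exceed 80%, so there is no figure to reproduce.

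**Inputs.** Windows L–U in weeks from injury (Table 1); follow-up times t after baseline (Study follow-up); baseline at b weeks after injury, 0 ≤ b ≤ 6 (Eligibility criteria, Table 1). Months are converted to weeks in two ways: the Table 1 window midpoints (4, 13, 26, 52) and calendar months (4.35, 13.04, 26.09, 52.18).

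**Case A: visits follow the Study follow-up text.** A punctual visit falls b + t weeks after injury and is in window if L ≤ b + t ≤ U. The lower limit is met in every row even at b = 0, so the condition is b ≤ U − t.

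| Visit | Window (weeks) | Latest b, midpoints | Latest b, calendar months | Latest b if limits mean completed weeks (add 0.86) |
|---|---|---|---|---|
| 1 month | 2–6 | 6 − 4 = 2 | 6 − 4.35 = 1.65 | 2.51–2.86 |
| 3 months | 11–15 | 15 − 13 = 2 | 15 − 13.04 = 1.96 | 2.81–2.86 |
| 6 months | 24–28 | 28 − 26 = 2 | 28 − 26.09 = 1.91 | 2.77–2.86 |
| 12 months | 48–56 | 56 − 52 = 4 | 56 − 52.18 = 3.82 | 4.68–4.86 |

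On midpoints, a woman enrolled by week 2 has 4 of 4 punctual follow-up visits in window; after week 2 and up to week 4, 1 of 4; after week 4, 0 of 4.

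**Cohort adherence with perfect attendance.** This needs a distribution for b, which the article does not give. The following are assumptions (midpoints):

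- Uniform over 0–6 weeks: (2/6 + 2/6 + 2/6 + 4/6)/4 = 1.667/4 = 42%. Counting baseline, which is always in window: (1 + 1.667)/5 = 53%.
- Uniform over 0–3 weeks: (2/3 + 2/3 + 2/3 + 1)/4 = 75%. Counting baseline: (1 + 3)/5 = 80%.
- Everyone within 2 weeks: 100%.

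Calendar months give 39% (51%) for 0–6 weeks and 71% (77%) for 0–3 weeks. Completed weeks give 53–56% (63–65%) and 92–96% (94–97%). Reading a month as 4 weeks (4, 12, 24, 48) gives 62.5% (70%) for 0–6 weeks, or 73% (79%) with completed weeks as well. That reading does not match the Table 1 midpoints of 13, 26 and 52.

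**How many late enrolments reach the 75% line?** Take midpoints and every other woman fully in window.

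- A fraction f enrolled at 2–4 weeks, each losing 3 of 4: 1 − 0.75f = 0.75, so f = 33%. Counting baseline: 1 − 0.6f = 0.75, so f = 42%.
- A fraction f enrolled after 4 weeks, each losing 4 of 4: 1 − f = 0.75, so f = 25%. Counting baseline: 1 − 0.8f = 0.75, so f = 31%.

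**Case B: visits follow Table 1.** The 3-month window opens at week 11, 5 weeks after the latest permitted baseline, so the 3-, 6- and 12-month windows are open to every participant. For the 1-month visit, the time left after a baseline at week b (b ≥ 2) is 6 − b weeks: 3 weeks at b = 3, 1 week at b = 5, none at b = 6. A woman with no time left loses one of her four follow-up visits.

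**The case against.** The strongest reply is that sites will work from Table 1. It labels its windows as targets, it defines adherence, and the stated alignment with routine fracture clinic visits fits an injury clock more naturally. On that reading the sentence in Study follow-up is loose wording and the 3-, 6- and 12-month windows are attainable by all. This stands as a limit on the finding: the lost windows in Case A arise only if visits are scheduled from baseline. It does not remove the contradiction, since two stated rules give different dates and the article does not say which governs. Nor does it resolve the 1-month overlap.

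Second, 6 weeks is an eligibility ceiling, and screening is aimed at new patients. Enrolment may be concentrated early, in which case the effect is small. This also stands. The uniform scenarios are illustrations, and they run from clear failure to meeting the criterion.

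Third, the consequences are bounded. Adherence is reported descriptively by site with confidence intervals, no passage makes a missed criterion an automatic stop, and the planned summaries of function, quality of life and stage of change do not use the 1-month visit. That is fair, but the plan also commits to declaring whether each criterion was met, and the 1-month visit is one of the visits counted.

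Finally, the article condenses a fuller protocol, and the process figure is not shown, so operational documents may already fix the origin. That cannot be judged from here. The conflict lies between two statements that the article does make.

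A reader might infer that women enrolled after 2 weeks will miss most of their windows, or that the study will fail its 75% criterion. The documents do not support either: the first depends on scheduling from baseline, the second also on an enrolment distribution that is not given.

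**Conclusion.** The inconsistency is real and affects how a primary feasibility criterion is scored: scheduling runs from baseline, scoring runs from injury, and nothing shown links them.

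Its size is conditional. If visits are scheduled from baseline, punctual visits are in window only for enrolment within about 2 weeks of injury (about 4 weeks for the 12-month visit). The 2-week cut-off is about 1.7–2 weeks with calendar months and up to about 2.9 weeks if the limits mean completed weeks. On midpoints, perfect attendance would score about 42% of follow-up visits (53% with baseline) under uniform enrolment over 0–6 weeks and 75% (80%) over 0–3 weeks, with little loss if nearly all women enrol within 2 weeks. If visits are scheduled by Table 1, what remains is the 1-month window lying inside the baseline window, which affects late enrollees and one of four follow-up visits.

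The finding is that the criterion is ambiguous as written and could penalise punctual visits. It is not a prediction that the criterion will be missed.

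**What to change.** Reconcile the Study follow-up text and Table 1 to one time origin, and score adherence against that origin. There are two ways to do it, and the choice is the sponsor's:

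- **Injury as origin.** This keeps the stated alignment with standard clinic visits. It needs a change to the sentence in Study follow-up and a rule for scoring the 1-month visit of late enrollees, for example not counting it as due when its window has closed or overlaps baseline.
- **Baseline as origin.** Table 1 is rewritten in weeks from baseline. This removes the overlap, at the cost of some of the alignment with clinic visits.

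In either case, report adherence alongside time from injury to enrolment, so that a low figure can be traced to late enrolment or to late visits. Eligibility already requires that interval to be known, so little or no extra data collection is involved.

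The cost is protocol and table wording plus the window check in the data system. No visits or patients are added. The change should be made before adherence is assessed.
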